### Statistical analysis

The incidence will be calculated as number of injuries per 1000 playing hours. The primary outcome of the study is the incidence of ACL injury. The secondary outcomes are the incidence of any acute knee injury (except contusion) and the incidence of severe knee injury (defined as injury resulting in absence of more than 4 weeks). All outcomes will be evaluated according to the mechanism of injury (contact or non-contact). The exposure and injuries for a team in the intervention group is calculated from the first interventional session performed during the season (matched with the same date to a team in the control group). All analyses will be performed both according to the intention-to-treat principle and according to per protocol. The analyses will be performed with group identity concealed. Clustering will be accounted for in the analyses and the intracluster correlation coefficient will be computed. A Cox regression model with cluster as a random effect will be performed as well as a multilevel mixed model analysis based on Poisson regression. The relative risk reduction (RRR) is calculated using the rate in the control group divided by the rate in the intervention group and will be reported as a ratio with 95% confidence interval. Covariates in the analyses will include age, menarche, previous knee injury, match frequency and match play with other teams than the player's own. The absolute risk reduction (ARR) is calculated using the rate in the control group minus the rate in the intervention group. The number needed to treat (NNT) will be calculated based on the ARR. All statistical tests will be 2-sided and a significance level of < 0.05 will be used.

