**Methods:**

In this cluster randomized trial 516 teams (309 clusters) in eight regional football districts in Sweden with female players aged 13–17 years were randomized into an intervention group (260 teams) or a control group (256 teams). The teams in the intervention group were instructed to do a structured warm-up program at two training sessions per week throughout the 2009 competitive season (April to October) and those in the control group were informed to train and play as usual. Sixty-eight sports physical therapists are assigned to the clubs to assist both groups in data collection and to examine the players' acute knee injuries during the study period. Three different forms are used in the trial: (1) baseline player data form collected at the start of the trial, (2) computer-based registration form collected every month, on which one of the coaches/team leaders documents individual player exposure, and (3) injury report form on which the study therapists report acute knee injuries resulting in time loss from training or match play. The primary outcome is the incidence of ACL injury and the secondary outcomes are the incidence of any acute knee injury (except contusion) and incidence of severe knee injury (defined as injury resulting in absence of more than 4 weeks). Outcome measures are assessed after the end of the 2009 season.

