Level C	Hold a ball over the head with straight arms. Perform a forward lunge and push back with the front leg and return to the starting position.	3 × 8–15
Level D	Hold a ball in front of the body with straight arms. Perform a sideway lunge and return to the starting position.	3 × 8–15
Pair-exercise	Teammate stands in front of you 5–10 meters away. Perform a forward lunge while making a throw-in with a ball.	3 × 8–15
6. Jump/landing	Make a jump with a soft landing. Stay briefly in the landing position.	
Level A	Stand on one leg with the knee slightly bent and hands on the hips. Make a short forward jump and land on the same foot. Jump backwards to the starting position.	3 × 8–15
Level B	Stand on two legs shoulder-wide apart with the hands on the back. Make a sideways jump and land on one foot. Alternate sides.	3 × 8–15
Level C	Take a few quick steps on the same spot and make a short jump straight forward landing on one foot.	3 × 5
Level D	Same as level C, but change direction and jump to one side (90 degrees turn). Alternate sides.	3 × 5
Pair-exercise	Teammate stands in front of you approximately 5 meters away. Make a two-legged jump while heading a football and land on two legs.	3 × 8–15

Exercises 1, 3, 5 and 6: Focus on knee over foot position

Exercises 2, 3, 4 and 5: Ensure abdominal and gluteal muscle contraction for increased lower back support

* Number of repetitions unless otherwise specified.

The clubs assigned to the intervention group were instructed to perform the exercises during the warm-up at two training sessions per week throughout the entire 2009 competitive season. The exercises are preceded by 5 minutes of low-intensity running and take about 10–15 minutes to complete after familiarization. Coaches and players are encouraged to watch each other closely and give feedback about the execution of exercises. All players start on the first level of difficulty (A) and the coach clears each player's progress to the next level when she performs the exercise with good control, mainly focusing on core stability and proper knee alignment.

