### Data collection

Data is collected during the competitive season from April until the end of the season in October (approximately 7 months). At the start of the study, a baseline form containing information about name, social security number, stature, body mass, menarche, family history of ACL injury, and the player's previous knee injuries and any current complaints is filled in by the player and parents/guardians. During the season, individual player exposure for each training session and match is reported by a coach or team leader on a computer-based registration form that is e-mailed to the research centre monthly. If a player has additional exposures outside the team, such as training or match play with a national team or with a senior team of the club, these are also registered on the exposure form. If a player sustains an acute knee injury during football training or match, the coach contacts the study therapist assigned to the club for evaluation of the injury. All acute knee injuries, except contusions, resulting in absence from play (time loss) are documented soon after the event by the study therapist on a standardized injury report form. If a severe knee injury is suspected, the player can be either advised to visit the nearest emergency department or referred to a study physician involved in the study. One physician experienced in diagnosing knee injuries is assigned to each regional district to assist the study therapists in the evaluation of severe knee injury. All players sustaining possible first-time ACL injuries (based on history and/or clinical examination) will be routinely examined with magnetic resonance imaging (MRI) by the study physicians to verify the diagnosis and to evaluate associated injuries. Suspected re-ruptures or secondary intraarticular injuries in knees with a previously reconstructed ACL will be assessed individually according to best practice. Injuries occurring at school, in other sports or during leisure time are not registered. Injuries are followed until full return to play or until 1 year post-injury.

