### Compliance

At the start of the study, coaches in the intervention group deliver a preliminary training schedule specifying the two weekly sessions where the structured warm-up program is planned to be carried out. Any subsequent changes in the schedule need to be reported to the study therapist. The coach documents on the exposure form if the program has been carried out as scheduled. The study therapists will make unannounced visits to their teams in the intervention group twice during the study period (once during the spring season and once during the autumn season) to monitor compliance to the program. Study therapists are encouraged to contact teams with low compliance (fewer than 6 prevention sessions over a 4-week period) to motivate them and increase their compliance.

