### Sample size

The sample size was based on previous data showing an average annual/seasonal incidence of ACL injury among female adolescent football players of 1.15% as reported in one prospective study [24] or in the control groups of previous knee injury prevention studies (Table 3) [14-17,19]. With a power of 80%, significance level of 5%, and an estimated risk reduction of 50% in the intervention group, randomization of approximately 4000 players to each group would be required [25].

**Table 3 T3:** Annual/seasonal incidence of ACL injury in prospective cohort or controlled intervention studies in adolescent female football used for the sample size calculation.

**Study**	**Population**	**Study design**	**Number of players in the control group**	**Number of players with ACL injury (%)**
Hewett et al., 1999 [15]	High school	Controlled trial	193	2 (1.04%)
Heidt et al., 2000 [14]	Age 14–18 years	Randomized controlled trial	258	8 (3.10%)
Powell & Barber-Foss, 2000 [24]	High school	Prospective cohort study	6 642	33 (0.50%)
Mandelbaum et al., 2005 [16]	Age 14–18 years	Controlled trial	3 818	67 (1.76%)
Pfeiffer et al. 2006 [17]	High school	Controlled trial	189	0
Steffen et al., 2008 [19]	Age 13–17 years	Randomized controlled trial	947	5 (0.53%)

ACL: Anterior Cruciate Ligament

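### The intention-to-treat analysis starts counting at each intervention team's first programme session, so its time origin depends on uptake and a team that never starts has no start date

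*Protocol article*

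**What the plan says.** The Statistical analysis section of the protocol article sets the start of counting: "The exposure and injuries for a team in the intervention group is calculated from the first interventional session performed during the season". For controls the start is "matched with the same date to a team in the control group"; how teams are matched is not stated. The next sentence reads: "All analyses will be performed both according to the intention-to-treat principle and according to per protocol". No separate start is given for the ITT analysis.

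Other sections describe a window that does not depend on uptake. Under Data collection: "Data is collected during the competitive season from April until the end of the season in October (approximately 7 months"). Under Intervention, clubs are assigned the programme at "two training sessions per week throughout the entire 2009 competitive season". Under Compliance, uneven use is foreseen: "Study therapists are encouraged to contact teams with low compliance (fewer than 6 prevention sessions over a 4-week period"). No section says what happens to a team that performs no session.

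**The concern.** An ITT comparison needs a time origin and a set of teams that are fixed independently of what teams do after allocation. Here the origin is the first use of the treatment. It occurs in one arm only and rests on session records kept by coaches who, as the Discussion says, cannot be blinded.

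Two consequences follow. Time before the first session is left out, although the assigned strategy covers the whole season and the data exist. And a team that never starts has no date from which anything can be counted. Such teams may differ from the others in organisation, training load and injury risk. Even if they do not, leaving them out turns an estimate of the effect of assignment into an estimate of the effect among starters. The rule governs the primary outcome, ACL injury, and both secondary outcomes.

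**Working it through.** **The plan's own figure.** Inputs from the Sample size section: control risk 1.15%, risk reduction 50% (so 0.575%), power 80%, significance level 5%; the Statistical analysis section makes tests two-sided. The two-proportion formula with pooled variance under the null is

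n = [1.960·√(2·p̄(1−p̄)) + 0.842·√(p₁(1−p₁) + p₂(1−p₂))]² / (p₁−p₂)², with p̄ = 0.008625.

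This gives 4059 per group, in line with the stated figure of about 4000. Power at 4000 per group is 79.4%, with 4000 × 0.0115 = 46 and 4000 × 0.00575 = 23 expected ACL injuries. The calculation does not involve the start rule, so a change of origin leaves it as it is.

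**Late starters.** Assume a constant injury rate over about 30.4 weeks (7 months), 4000 players per arm, and equal truncation of both arms through the matched date. A mean delay of w weeks keeps a share 1 − w/30.4 of the season.

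| Mean delay (weeks) | Season kept | Expected ACL injuries, control / intervention | Power |
|---|---|---|---|
| 0 | 100% | 46 / 23 | 79.4% |
| 1 | 97% | 44.5 / 22.2 | 78.1% |
| 2 | 93% | 43.0 / 21.5 | 76.7% |
| 4 | 87% | 39.9 / 20.0 | 73.6% |
| 8 | 74% | 33.9 / 16.9 | 66.4% |

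The measurable cost of late starts is lost information. The delays are assumptions; the protocol gives none.

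**Never-starters.** All ratios here are intervention over control (the plan reports the inverse). Let q be the share of intervention-arm exposure in teams that never start, k their baseline risk relative to starters, and RR the rate ratio in starters. Assume no effect in never-starters, and that the control arm keeps its full mix of teams, so that its rate is proportional to D = (1−q) + qk.

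- ITT ratio = [(1−q)·RR + qk] / D
- Ratio under the rule, if never-starters contribute nothing = RR / D
- ITT ratio minus rule ratio = q(k − RR) / D

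The difference is positive, and the programme is flattered, when k exceeds RR. It is zero when k equals RR and runs against the programme when k is below RR.

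| RR | q | k | D | ITT ratio | Ratio under the rule |
|---|---|---|---|---|---|
| 0.50 | 0.05 | 1 | 1.00 | 0.525 | 0.50 |
| 0.50 | 0.10 | 1 | 1.00 | 0.55 | 0.50 |
| 0.50 | 0.20 | 1 | 1.00 | 0.60 | 0.50 |
| 0.50 | 0.20 | 2 | 1.20 | 0.667 | 0.417 |
| 0.50 | 0.20 | 0.5 | 0.90 | 0.556 | 0.556 |
| 1.00 | 0.20 | 2 | 1.20 | 1.00 | 0.83 |
| 1.00 | 0.20 | 0.5 | 0.90 | 1.00 | 1.11 |

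For example, the fourth row is (0.8 × 0.50 + 0.2 × 2) / 1.20 = 0.667 against 0.50 / 1.20 = 0.417. The values of q and k are assumptions; RR = 0.50 is the effect assumed in the Sample size section.

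**The case against.** Four points on the other side carry weight.

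- **Exclusion is not stated.** A reader might infer that the plan deliberately drops never-starting teams. It does not say so. The sentence on ITT could be read as keeping every randomised team, and a full analysis plan could supply a fallback date. What stands is that the published rule gives such a team no start date.
- **Late-start time is not cut in one arm only.** A reader might infer a one-sided removal of early injuries. The matched date cuts control time too, which aligns calendar time. What remains is the loss of recorded data and an origin driven by uptake. One-sided loss can arise only for never-starters.
- **The matching is undescribed, not impossible.** Teams "were randomized into an intervention group (260 teams) or a control group (256 teams"), and the Randomization section describes no pairing. Those counts rule out strict one-to-one pairs, but the text does not require such pairs, so they are no contradiction.
- **Non-start may be rare.** Teams with fewer than two scheduled weekly sessions were not included, coaches were trained before the start, a session schedule is delivered at the outset, and therapists visit teams and are encouraged to contact those with low compliance. These steps make short delays plausible, and a delay of 1–2 weeks costs little power. They do not exclude non-start, and the Background itself calls poor compliance a well-known problem.

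**Conclusion.** The point holds. As written, the ITT analysis takes its time origin from uptake of the programme. It discards recorded early-season data in both arms and leaves never-starting teams without a start date. That conflicts with the ITT principle stated in the same section, whatever the number of late or absent starters turns out to be.

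The size cannot be fixed from the protocol, which gives neither start delays nor a share of never-starters. If never-starters are lost and the programme works as assumed, equal baseline risk and a 10–20% share give 0.50 instead of 0.55–0.60. Under a true null with a 20% share, the ratio lies between 0.83 and 1.11 as the never-starters' relative risk goes from 2 to 0.5.

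A reader might conclude that the rule generally favours the programme. The protocol does not support that: the direction turns on whether k exceeds RR, and nothing in it fixes k.

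**What to change.** For the ITT analysis, count exposure and injuries in both arms from one fixed calendar date that does not depend on programme use: the April 2009 opening of data collection. Include every randomised team with data, whether or not it ran the programme. A team's first registered activity would be a weaker choice of origin, because it again depends on what teams do and report after randomisation. Keep the first-session and matched-date origin for the per-protocol analysis or a sensitivity analysis only.

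The cost is a change of wording in the analysis plan. Data collection already runs from April, and the sample size is unaffected. The downside is that time before the first session slightly dilutes the ITT effect.

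### The quantity called relative risk reduction is the control rate divided by the intervention rate: an inverted rate ratio, not a relative reduction

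*Protocol article*

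**What the plan says.** The Statistical analysis section of the protocol article sets incidence on an exposure basis: "The incidence will be calculated as number of injuries per 1000 playing hours". It then gives formulas for two effect measures.

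- Relative: "The relative risk reduction (RRR) is calculated using the rate in the control group divided by the rate in the intervention group". The sentence adds that the result "will be reported as a ratio with 95% confidence interval".
- Absolute: "The absolute risk reduction (ARR) is calculated using the rate in the control group minus the rate in the intervention group". From this follows: "The number needed to treat (NNT) will be calculated based on the ARR".

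The same section plans a Cox model with a random cluster effect and a multilevel Poisson model.

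The Sample size section expresses the design effect as "an estimated risk reduction of 50% in the intervention group", starting from "an average annual/seasonal incidence of ACL injury among female adolescent football players of 1.15" per cent. Nothing elsewhere in the article adds a subtraction from 1 to the relative measure or gives it another meaning.

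**The concern.** The name and the formula describe different quantities. A relative risk reduction has its null at 0 and cannot exceed 1 (100%). Control rate over intervention rate has its null at 1 and no upper bound. If the rule is followed literally, the published figure and its interval carry a name that does not fit their scale.

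Direction adds to the difficulty. With control as the reference group, as is usual, the Poisson and Cox models give intervention-over-control ratios, which fall below 1 under benefit. The quantity defined here rises above 1 under benefit. One report could then show two relative measures of the same effect on opposite sides of 1. Harm would appear as a value below 1 under the label of a reduction, which a reader used to the conventional direction could take as protective. The Background section itself mentions an earlier prevention study in which risk may have risen in the trained group, so that case is worth guarding against.

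**Working it through.** **Inputs.** Control risk 1.15% per season, a 50% reduction, 80% power and 5% significance (Sample size); two-sided tests and the two effect formulas (Statistical analysis).

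**Step 1: what the Sample size section means by a 50% reduction.** Take control risk 0.0115 and intervention risk 0.0115 × 0.5 = 0.00575. The unpooled two-proportion formula is

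n = (1.960 + 0.8416)² × [0.0115 × 0.9885 + 0.00575 × 0.99425] / (0.00575)² = 4056 per group.

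With the pooled variance under the null it is 4059. Both match the stated figure of about 4000. The section therefore uses the term in its ordinary sense, 1 − intervention/control.

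**Step 2: apply the Statistical analysis formula to that effect.**

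- Stated formula: 1.15 / 0.575 = 2.0
- Usual rate ratio: 0.575 / 1.15 = 0.50
- Relative risk reduction: 1 − 0.50 = 0.50

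These are seasonal risks, whereas the trial will use rates per 1000 hours. The example shows how the formulas relate; it does not predict the trial's result.

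**Step 3: other effects.** The control rate is set to 1.0 and the intervention rates are assumed for illustration.

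| Intervention rate | Stated formula (control/intervention) | Rate ratio (intervention/control) | Relative risk reduction |
|---|---|---|---|
| 0.25 | 4.0 | 0.25 | 75% |
| 0.50 | 2.0 | 0.50 | 50% |
| 0.80 | 1.25 | 0.80 | 20% |
| 1.00 | 1.0 | 1.00 | 0% |
| 1.25 | 0.80 | 1.25 | −25% |
| 2.00 | 0.50 | 2.00 | −100% |

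A stated value of 0.50 thus corresponds to a doubling of the rate, while a relative risk reduction of 0.50 is a halving.

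**Step 4: the interval.** If the stated ratio has limits L to U, the rate ratio has limits 1/U to 1/L, and the relative risk reduction has limits 1 − 1/L to 1 − 1/U. With assumed limits, a stated 2.0 (1.0 to 4.0) becomes a rate ratio of 0.50 (0.25 to 1.0) and a relative risk reduction of 0.50 (0 to 0.75).

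**Step 5: what does not change.** The log of control/intervention is minus the log of intervention/control, with the same standard error, so the two-sided p-value is identical. The model fits do not use the formula. The absolute reduction is a separate difference, correctly signed, and the number needed to treat rests on it. Step 1 did not use the formula, so the sample size stands.

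**The case against.** The strongest defence is that the sentence itself announces a ratio and states its numerator and denominator. On that reading the authors intended a rate ratio and gave it the wrong name. Control over intervention also orders the groups as the absolute measure does, and placing the intervention group in the numerator is only a convention. No information is lost, because the relative risk reduction equals 1 − 1/ratio.

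Much of this stands. The direction alone, once stated, would not be an error, and a drafting slip is the likeliest explanation, since the Sample size section uses the term conventionally. The name is still wrong, and the quantity still runs against the usual direction of the model ratios.

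A second defence is that the formula names only an ingredient of a fuller calculation. The text does not support this. The absolute measure is introduced with the same construction, and there the wording is the complete formula. Nor is this a detail that a condensed article leaves out, because the formula is stated.

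Two stronger readings are tempting and should be resisted. A reader might infer that the trial's headline effect would be misstated, but the article does not name this measure as the main estimate; it also plans two models, an absolute reduction and a number needed to treat. A reader might also fear that a null result of 1.0 would be taken as a 100% reduction. The statement that the figure is reported as a ratio makes that unlikely.

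**Conclusion.** The definition is wrong as written and should be corrected. What it calls a relative risk reduction is the reciprocal of the usual rate ratio: 2.0 instead of 0.50 at the planned effect, and 1 instead of 0 at the null. The Sample size and Statistical analysis sections therefore attach different meanings to the same idea.

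The consequence is limited to how one relative effect and its 95% interval are named and scaled. It does not reach hypothesis tests, model estimates, absolute measures or the sample size.

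The arithmetic rests only on the article's formula and planning figures. The remark that the models would run in the opposite direction assumes control as the reference group, which the article does not state.

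**What to change.** Replace the sentence with one that does two things:

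1. Report the rate ratio, intervention over control, with a 95% confidence interval from the cluster-adjusted model.
2. Define the relative risk reduction as 1 minus that rate ratio, with confidence limits equal to 1 minus the rate-ratio limits, lower and upper exchanged.

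The definitions of the absolute reduction and the number needed to treat need no change on this account. The cost is one sentence, with no new data, no additional analysis and no change to the sample size.

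### Two covariates recorded during the season, match frequency and match play with other teams, are listed for the treatment models, so the adjusted effect can be biased in either direction by an amount the protocol does not fix

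*Protocol article*

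**What the plan says.** The Statistical analysis section of the protocol article names two models: "A Cox regression model with cluster as a random effect will be performed as well as a multilevel mixed model analysis based on Poisson regression". Two sentences later, between the definitions of the relative and the absolute risk reduction, it gives one covariate list for all analyses: "Covariates in the analyses will include age, menarche, previous knee injury, match frequency and match play with other teams". Nothing there reserves the last two covariates for a risk-factor analysis.

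The Data collection section says where each variable comes from. At the start of the study, players and parents complete "a baseline form containing information about name, social security number, stature, body mass, menarche, family history of ACL injury", together with previous knee injuries and current complaints. Match play is not on that list. It is recorded later: "During the season, individual player exposure for each training session and match is reported by a coach or team leader". Play elsewhere goes on the same monthly form: "If a player has additional exposures outside the team, such as training or match play with a national team or with a senior team".

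The Background explains the interest in these two variables: high match frequency and senior-level match play are described there as speculated risk factors.

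**The concern.** Age, menarche and previous knee injury describe the player at the start, and the programme cannot have changed them. The two match variables are observed while the programme is running. That raises two separate problems.

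- **Effect of allocation.** Players and coaches know their group. If the programme alters availability or selection for matches, match play lies on the path from allocation to injury. Adjusting for it removes that part of the effect.
- **Effect of the outcome.** Every counted injury is a time-loss injury (Table 1), so it reduces the matches played afterwards. A whole-season measure is then partly a result of the endpoint it is used to explain.

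Randomisation already deals with baseline confounding, and a variable measured after allocation cannot confound allocation. At stake is the meaning of the adjusted hazard or rate ratio: it may no longer describe the effect of being assigned to the programme.

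**Working it through.** **Timing of each covariate**

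| Covariate | Source in the article | Timing |
|---|---|---|
| Age | Birth years in Club recruitment | Fixed before the season |
| Menarche, previous knee injury | Baseline form | Start of study |
| Match frequency | Monthly exposure form | During the season |
| Match play with other teams | Same exposure form | During the season |

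The in-season timing of the last two rows is inferred: they are absent from the baseline form and present on the exposure form, and no other source is described.

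**The plan's own figures.** The plan gives no figure for this adjustment. Its sample size uses no covariates and is not affected. For 1.15% against 0.575%, two-sided 5% and 80% power, (1.96 + 0.8416)² × (0.0115 × 0.9885 + 0.00575 × 0.99425) / 0.00575² gives about 4,056 per group (4,059 with pooled variance), in line with the stated figure of approximately 4,000.

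**Inputs for an illustration.** From the article: control risk 1.15% and a halving. Assumed, because the article does not give them: 28 weeks, a mean of 1 match per week, 3 training hours per week, 1.2 hours per match, hazard proportional to matches, and a 10% change in match play caused by the programme. The true ratio per match is set at 0.5.

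**Hand check, injuries per playing hour.** Weekly hours are 3 + 1.2 × 1 = 4.2 in the control group.

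- With 10% more matches, the intervention group has 3 + 1.2 × 1.1 = 4.32 hours. The unadjusted ratio is 0.5 × 1.1 × 4.2 / 4.32 = 0.535.
- With 10% fewer, it has 3 + 1.2 × 0.9 = 4.08 hours. The ratio is 0.5 × 0.9 × 4.2 / 4.08 = 0.463.

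Full adjustment for the weekly match rate takes both to about 0.50, shifts of roughly 0.035 and 0.037. Simulated shifts are somewhat smaller, because an observed weekly rate carries chance variation.

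**Simulated Poisson models with a log-hours offset**

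| Covariate entered | Change in matches | Unadjusted | Adjusted |
|---|---|---|---|
| Matches per week | none | 0.508 | 0.508 |
| Matches per week | +10% | 0.521 | 0.502 |
| Matches per week | −10% | 0.472 | 0.490 |
| Season count | none | 0.508 | 0.515 |
| Season count, CV 0.3 | +10% | 0.53 | 0.76 |
| Season count, CV 0.7 | +10% | 0.55 | 0.60 |
| Season count, SD 0.3 | −10% | 0.47 | 0.32 |

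The matches-per-week rows and the season-count row without a change used 400,000 players per arm. At +10% that is about 4,600 control and 2,530 intervention injuries, so the log ratio has a standard error near √(1/4600 + 1/2530) = 0.025, or about 0.013 on the ratio. The simulated 0.521 and 0.472 therefore agree with the hand-checked 0.535 and 0.463.

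**Two sensitivities**

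- **Spread of match play.** The season-count result depends heavily on how much match play varies between players. A single run at CV 0.14 went from 0.56 to 1.16, so no one figure should be quoted as the size.
- **Denominator.** With follow-up time instead of hours, a shift of 0.1 in log match frequency moved the ratio from 0.560 to 0.508 (increase) or from 0.455 to 0.503 (decrease), about 0.05. This is relevant if the Cox model runs on calendar time.

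**The case against.** Several points on the other side have force.

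- **A frequency is a rate.** The large shifts need a season count, which the article does not name. On the natural reading the shift is small. This stands, and the small figures should lead.
- **Nothing in the article says the programme changes match play.** It is a 10 to 15 minute warm-up at two sessions a week, and much of match frequency plausibly follows the league schedule. This stands too: without such a change the shift is about zero.
- **The outcome is already a rate per playing hour**, so it conditions on exposure after allocation. Match risk is described as considerably higher than training risk, and total hours do not capture that mix. This is a fair reason to examine match play, but a separate or sensitivity model can do so without altering the treatment estimate.
- **The risk reductions and the number needed to treat are computed from group rates**, and may be unadjusted. Yet the text does not place them above the models, nor make a model without these covariates primary.
- **This is a condensed article.** The definition of match frequency, and any time-updating of it, may be in a fuller plan. Their absence is not held against the trial. The point concerns the adjustment that is stated.

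A reader might infer that the trial's main result is bound to be biased, or that a true halving would be hidden. The documents support neither. Both would need the count definition, little variation between players and an actual effect of the programme on match play, and the article establishes none of these.

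**Conclusion.** The point holds as a possible bias of unknown size. The article lists two in-season variables as covariates in the analyses that estimate the treatment effect. Allocation may influence them, and injury cuts them short.

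For a 10% change in match play, the adjusted hourly rate ratio moves by about 0.02 to 0.03 when the covariate is matches per week. It moves much further, in the opposite direction, when the covariate is an injury-truncated season count. With no change in match play, it hardly moves. These figures rest on the assumed exposure pattern, a hazard proportional to matches and the assumed spread between players. That the adjustment is stated is clear from the text. How much it matters is not, and the reading closest to the wording gives a small effect. The wording should still be changed, because nothing in it excludes the harmful form.

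**What to change.** In the Statistical analysis section, limit the covariates in the Cox and Poisson treatment models to those already listed that are fixed at baseline: age, menarche and previous knee injury. Move match frequency and match play with other teams to a separate risk-factor or sensitivity model, with both entered as values updated over time up to the injury date and not as season totals. This keeps the risk-factor question from the Background and protects the randomised comparison.

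The cost is a change of wording and a little more analysis work. No new data are needed, and the sample size is unchanged.
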